### Study procedures

Clinical evaluation will occur at two weeks (7–21 days window), six weeks (4–8 weeks window), three months (11–15 weeks window), six months (6–7 months window), and 12 months (12–14 months window) after start of treatment [Table 1]. These visits are standard of care for the targeted patient group. At each follow-up visit, the research coordinator or research assistant will ascertain patient status (*i.e.*, adverse events/complications, secondary interventions, etcetera, and will verify information within medical records).

**Table 1 T1:** Schedule of events

**Radiographs & events**	**Screening**	**Enrolment**	**Baseline**	**Post**	**2 weeks**	**6 weeks**	**3 months**	**6 months**	**12 months**
				**surgery**	**(7–21 d)**	**(4–8 we)**	**(11–15 we)**	**(6–7 mo)**	**12-14 mo)**
X-ray	X						X^1^	X^1^	X^1^
Screening	X								
Informed consent		X							
Baseline data			X						
Surgical report form				X					
DASH					X	X	X	X	X
Pain (VAS)					X	X	X	X	X
SF-36					X	X	X	X	X
EQ-5D					X	X	X	X	X
Clinic FU					X	X	X	X	X
Range of motion					X	X	X	X	X
Secondary interventions					X	X	X	X	X
Complications					X	X	X	X	X
Health care consumption					X	X	X	X	X
ADL/work resumption					X	X	X	X	X
Physical therapy					X	X	X	X	X
Constant score						X	X	X	X
Early withdrawal					*	*	*	*	*

^1^X-rays will be taken according to local protocol; all X-rays after three months will be analyzed. The six-month X-ray is needed for assessing fracture healing. If no signs of healing are seen at six months, the 12-month X-ray is also required.

*Only at time of withdrawal.

At each follow-up visit, the range of motion of the shoulder and elbow will be measured using a goniometer by a physician or research assistant. In addition, patients will be asked to complete the questionnaires relating to disability (DASH score including optional modules), pain (VAS), health-related quality of life (SF-36, EQ-5D), health care consumption and production loss. From six weeks onwards, the research coordinator or research assistant will determine the Constant score.

At each clinical follow-up visit, anterior-posterior and lateral radiographs are generally routinely obtained. All images available from three months onwards will be analyzed. Apart for the 6-month follow-up, during which X-rays are needed for assessing signs of nonunion, local radiographical protocols will apply. For this reason, the follow-up at six month should not be done earlier. In case no radiographic healing is seen at six months, an X-ray at 12 months is also required. At the last visit, the surgeon or researcher will also document any secondary intervention that is planned for the patient.

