## Abstract

**Background:**

Fractures of the humeral shaft are associated with a profound temporary (and in the elderly sometimes even permanent) impairment of independence and quality of life. These fractures can be treated operatively or non-operatively, but the optimal tailored treatment is an unresolved problem. As no high-quality comparative randomized or observational studies are available, a recent Cochrane review concluded there is no evidence of sufficient scientific quality available to inform the decision to operate or not. Since randomized controlled trials for this injury have shown feasibility issues, this study is designed to provide the best achievable evidence to answer this unresolved problem. The primary aim of this study is to evaluate functional recovery after operative versus non-operative treatment in adult patients who sustained a humeral shaft fracture. Secondary aims include the effect of treatment on pain, complications, generic health-related quality of life, time to resumption of activities of daily living and work, and cost-effectiveness. The main hypothesis is that operative treatment will result in faster recovery.

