### Recruitment and consent

Eligible persons presenting to the ED with a humeral shaft fracture will be informed about the trial at the ED. After an explanation of the study, they will receive information and a consent form from the attending physician, the clinical investigator, or a research assistant. Patients meeting all inclusion criteria and none of the exclusion criteria will be included while they are still at the ED or at the time of their first outpatient visit.

As with many surgical trials, patients and surgeons cannot be blinded for treatment. In order to reduce bias, a research physician or research assistant will perform the follow-up measurements using a standardized protocol. Radiographs can also not be blinded for treatment; however, evaluating radiographs in duplicate by two trauma surgeons independently will improve reliability of fracture healing assessment. In case of disagreement they will discuss the results until they reach consensus. Finally, the analysis will be performed by a statistician without knowledge of treatment.

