### Study population

All persons aged 18 years or older presenting to the ED with a humeral shaft fracture (AO type 12A or 12B) are eligible for inclusion [33]. The AO type 12C fractures will be excluded due to their low occurrence rate. Humeral shaft fractures are defined as fractures located in the area between the surgical neck and the area immediately above the supracondylar ridge.

Patients meeting the following inclusion criteria are eligible for enrolment:

1. Adult men or women aged 18 years or older (with no upper age limit)

2. A fracture of the humeral shaft, AO class 12A or 12B (confirmed on X-ray)

3. Operation within 14 days after presentation to the ED (if this is the treatment of choice)

4. Provision of informed consent by patient

If any of the following criteria applies, patients will be excluded:

1. Patients with concomitant injuries affecting treatment and rehabilitation of the affected arm

2. Patients with a humeral fracture treated with an external fixator

3. Patients with a pathological, recurrent or open humeral shaft fracture

4. Patients with neurovascular injuries requiring immediate surgery (excl. radial nerve palsy)

5. Additional traumatic injuries of the affected arm that influence upper extremity function

6. Patients with an impaired upper extremity function (*i.e.*, stiff or painful arm or neurological disorder of the upper limb) prior to the injury

7. Retained hardware around the affected humerus

8. Patients with rheumatoid arthritis

9. Bone disorder which may impair bone healing (excluding osteoporosis)

10. Patients incapable of ensuring follow-up (*e.g.*, no fixed address or cognitive impairment)

11. Insufficient comprehension of the Dutch language to understand the rehabilitation program and other treatment information, as judged by the treating physician of researcher

Exclusion of a patient because of enrolment in another ongoing drug or surgical intervention trial will be left to the discretion of the attending surgeon on a case-by-case basis.

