### Intervention

The decision on treatment will be left to the discretion of the attending surgeon. The choice will be between operative and non-operative treatment. Also, the rehabilitation after treatment will not be standardized, but will be provided as in real life. Although this may create some heterogeneity across groups, it will improve the generalizability of the study results.

If a surgeon decides to operate the patient, the choice between plate osteosynthesis or intramedullary nailing will be left to the treating surgeon. No restrictions will be applied to the approach for reduction and fixation of the fracture, *e.g.*, open or closed, antegrade or retrograde. The type and brand of the materials as well as the use of cerclage wires and other elements of the surgery will be left to the surgeon, local availability and expertise. Critical elements of the operative treatment will be recorded (*e.g.*, type of implant, identification of the radial nerve, surgical approach, operative delay, duration of surgery) and the effect on outcome will be assessed.

In order to maximize generalizability, the type of non-operative treatment will also be left to the attending surgeon. Usually it consists of a splint, plaster, collar and cuff or hanging cast for 1–2 weeks, followed by a Sarmiento brace for 4–6 weeks. Critical elements of this treatment will be recorded and the effect on outcome will be assessed.

Due to a lack of evidence favoring a particular approach, the physical therapy and rehabilitation program will be recorded but not standardized. This will improve generalization of the study results.

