The range of motion (ROM) of the shoulder (*i.e.*, abduction and forward flexion) and the elbow joint (*i.e.*, flexion and extension) will be measured using a goniometer. Both sides will be assessed separately, and the loss of ROM will be calculated.

Complications will be recorded from medical charts. Complications may include: 1) surgical site infection; 2) wound dehiscence; 3) skin problems (*e.g.*, skin at risk, skin necrosis); 4) dystrophia; 5) radial nerve palsy; 6) malunion; 7) implant failure (screw breakout); 8) cuff pathology; 9) secondary fracture dislocation; or 10) non-union. Non-union is defined as a failure to heal at twenty-six weeks post fracture with no progress towards healing seen on the most recent radiographs [37].

Secondary intervention within one year of initial treatment to promote fracture healing, relieve pain, treat infection, or improve function will be recorded from medical charts. Interventions will be categorized as: 1) osteosynthesis with or without bone grafting; 2) implant exchange with or without bone grafting; 3) implant removal; 4) incision and drainage for superficial surgical site infection; or 5) incision and drainage for deep surgical site infection. The indication and admission duration for all intervention will also be recorded.

Presence of radiographic healing will be determined using X-rays. Fracture consolidation is defined when one of the three criteria listed is present; 1) bridging of fracture by callus/bone trabeculae or osseous bone; 2) obliteration of fracture line/cortical continuity; or 3) bridging of fracture at three out of four cortices.

The time to resumption of work and activities of daily living will be recorded using a custom-made questionnaire.

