b) Injury related variables: affected side, mechanism of injury, fracture classification according to the AO classification system, additional injuries, and admission duration.

c) Intervention-related variables: time between injury and start of treatment, days of collar and cuff, sling or plaster, time between injury and start of physical therapy, and number of physical therapy sessions.

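### DASH visits are timed from start of treatment while surgery may follow up to 14 days after presentation, so the groups may be compared at different average times since injury

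*Protocol article*

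**What the plan says.** - **Visit clock.** Study procedures sets five visits, from two weeks to 12 months, and closes the list with "months window) after start of treatment". Table 1 schedules the DASH at all five.
- **Surgical delay.** Inclusion criterion 3 under Study population reads "Operation within 14 days after presentation to the ED (if this is the treatment of choice". It binds only patients chosen for surgery.
- **Non-operative treatment.** The Intervention section describes the first step: "Usually it consists of a splint, plaster, collar and cuff or hanging cast for 1–2 weeks". A brace follows. No date is named as the start, and no waiting period is described.
- **Enrolment.** Under Recruitment and consent, patients "will be included while they are still at the ED or at the time of their first outpatient visit". Enrolment can therefore precede the day on which criterion 3 is settled.
- **Delay as data.** Outcome measures lists "c) Intervention-related variables: time between injury and start of treatment". The Intervention section also names operative delay among the surgical elements whose effect on outcome will be examined.
- **Analysis.** The primary mixed model takes covariates from the intrinsic and fracture-related variables. The delay is in the third, intervention-related class. The variables named for the propensity score do not include it.
- **Aim.** The Abstract states: "The main hypothesis is that operative treatment will result in faster recovery".

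**The concern.** When the hypothesis concerns speed of recovery, the time origin is part of the estimand. If one group's clock starts at or near presentation and the other's at an operation days later, a visit with the same label falls at different times since fracture. DASH falls as patients recover, so the group measured later can look better for that reason alone. Covariate adjustment or matching on baseline characteristics does not remove this, because the difference lies in when the outcome is measured. The powered contrast, DASH at three months, lies on the part of the curve where recovery may still be under way.

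A second issue has the same source. Criterion 3 depends on an event that may come after enrolment, and it applies to one group only. The article does not say how a patient chosen for surgery but operated on after day 14, or not at all, is handled.

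**Working it through.** **1. The plan's own figure.** Sample size calculation gives DASH 16 (SD 16) for non-operative and 10 (SD 10) for operative treatment, a difference of 6, with two-sided α 0.05 and power 0.80. I read both means as three-month values.

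n = (16² + 10²)(1.960 + 0.842)² / 6² = 77.6, so 78 per group, as stated. The 6 points and the SDs serve below as the yardstick.

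**2. Lag as a share of nominal follow-up.** With non-operative treatment starting at presentation (assumed), the largest lag is 14 days. That is 14/14 = 100% of two weeks, 14/42 = 33% of six weeks, 14/91 = 15% of three months, 14/182 = 8% of six months and 14/365 = 4% of 12 months. The group shift depends on the mean lag, which is not given, so I take 3, 7 and 14 days.

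**3. Conversion to DASH points (assumed curves).** The documents give no recovery curve. I use DASH(t) = P + A·exp(−kt), with t in weeks, through an assumed value at week 2 and the plan's 16 at week 13:

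- k = ln[(DASH₂ − P)/(16 − P)]/11
- A = (16 − P)·exp(13k)

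| Week-2 DASH (assumed) | Plateau P (assumed) | k |
|---|---|---|
| 45 | 10 | 0.160 |
| 50 | 8 | 0.151 |
| 60 | 5 | 0.146 |

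The shift from a lag L is DASH(t) − DASH(t + L). The range over the three curves is:

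| Nominal visit | L = 3 days | L = 1 week | L = 2 weeks (maximum) |
|---|---|---|---|
| 2 weeks | 2.3–3.3 | 5.2–7.5 | 9.6–14.0 |
| 6 weeks | 1.2–1.9 | 2.7–4.2 | 5.1–7.8 |
| 3 months (13 weeks) | 0.4–0.7 | 0.9–1.5 | 1.6–2.8 |
| 6 months (26 weeks) | 0.05–0.10 | 0.1–0.2 | 0.2–0.4 |
| 12 months (52 weeks) | <0.01 | <0.01 | <0.01 |

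Example: for the first curve at 13 weeks with L = 2, the shift is (16 − 10)(1 − e^(−0.3206)) = 6 × 0.274 = 1.65.

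As a share of the planned 6 points, the three-month shifts are 7–11%, 15–25% and 27–47%. The last range needs a mean lag at the 14-day limit.

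**4. Effect on the test.** With no true effect and a shift b, SE = √(356/n), which is 2.14 for n = 78 and 1.33 for n = 200. The rejection probability is 1 − Φ(1.96 − b/SE) + Φ(−1.96 − b/SE).

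| Shift b | n = 78 per group | n = 200 per group |
|---|---|---|
| 0.43 (3 days at 1 point/week) | 5.5% | 6.2% |
| 1.0 (7 days at 1 point/week) | 7.5% | 11.6% |
| 2.0 (14 days at 1 point/week) | 15.5% | 32.3% |

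The larger target sample makes a spurious signal more likely. The three curves fall by 0.96, 1.21 and 1.61 points per week at 13 weeks (k(16 − P)), so 1 point per week is near their lower end.

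**The case against.** **The plan does attend to delay.** It records the time to treatment and commits to assessing operative delay. This stands, and it would be wrong to say that the plan ignores delay. But assessing delay among operated patients does not align the two groups on time since injury. The propensity list is introduced as non-exhaustive, and the article does not say how time enters the mixed model. The full plan may settle both, although the visit clock and the covariate classes are stated here.

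**Non-operative treatment may not start at presentation.** This stands as a limit. The text suggests an early start but does not state one. If a site dated treatment from the brace, the lag would shrink or reverse.

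**The curve is assumed.** This stands. The calculation also treats the days before surgery as ordinary recovery and gives surgery no early effect of its own on DASH. The figures at two and six weeks are therefore the largest and the least secure.

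**Stronger readings that the documents do not support:**

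- A reader might infer that each operated patient has healed longer at each visit. Some may be operated on at once, and the visit windows are wide (7–21 days at the first visit). The lag is a difference in averages, and 14 days is its upper limit.
- A reader might infer that the 14-day condition removes worse patients and so favours surgery. Nothing says that patients delayed past day 14 do worse or are removed. The criterion also plausibly separates primary surgery from surgery after failed non-operative care.
- A reader might see a contradiction in non-union having its own clock ("Non-union is defined as a failure to heal at twenty-six weeks post fracture"). It does not conflict with the visits: the six-month visit may not be held early, so it falls at about 26 weeks after fracture or later.

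**Conclusion.** The point holds in a limited form. As written, the plan lets operated patients be further from injury on average at the same nominal visit, by at most about 14 days, and no described analysis aligns the groups. This rests on non-operative treatment starting at or near presentation. If it does, the shift runs towards the trial's hypothesis.

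The size cannot be derived from the documents. At three months it runs from under one DASH point for a mean lag of a few days to just under half of the planned difference at the limit, on assumed curves. It is larger but less certain at two and six weeks, and small at six and 12 months. The one-sided 14-day condition leaves room for selection after enrolment, of unknown direction and size. The correction is cheap and worth making before analysis.

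**What to change.** - **Time variable.** In the primary mixed model, use actual days since injury (or since ED presentation) in both groups, with a form flexible enough for a curved recovery. Read the three-month contrast at the same time since injury, for example 13 weeks. Do the same for the models of the Constant, SF-36 and EQ-5D scores.
- **Sensitivity analysis.** Keep timing from start of treatment, and define that start for both groups.
- **Groups.** Analyse patients by the treatment decision recorded at enrolment. Do not drop or reclassify a patient in the analysis because surgery fell after day 14 or did not take place. Report how many such patients there were.
- **Report** the distribution of the time from injury to treatment in each group, so that readers can judge the lag.

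The cost is analysis wording and one derived variable: the recorded delay plus the interval from start of treatment to the visit. The article lists the delay but not visit dates or a dated treatment decision, so confirm that the case report form holds both. The downside is that observed days fit the nominal visit windows less neatly. No visit, procedure or treatment changes.

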### Sample size calculation

Calculation of the required sample size for the primary analysis is based on the assumption that the mean DASH in the non-operative group will be 16, with a Standard Deviation (SD) of 16 [8]. We expect less disability (*i.e.*, lower DASH score) at three months in the operative group; the expected DASH score in the operative group will be 10 (SD 10) [8]. A two-sided test with an α level of 0.05 and a β level of 0.2 requires 78 patients in every group. In order to account for loss of patients due to mortality (10%) and loss-to-FU (10% anticipated based upon previous studies by the research team), a sample size of 95 patients per group is needed.

Results of a retrospective study assessing clinical outcome of humeral shaft fractures, showed that 45-55% of all AO-subclasses were treated operatively [18]. In order to assess whether functional outcome scores differ between the fracture subtypes, a minimum of 2x20 patients per fracture subtype is sufficient. In order to achieve that, we need to include until at least 200 patients in both the operative groups and the non-operative group.

For the secondary analysis, some patients may be lost during the propensity score matching. Although we do not have a-priori data to determine how many patients will be lost, the 400 targeted patients will be more than sufficient.

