## Discussion

The HUMMER trial will study outcome after operative versus non-operative treatment of humeral shaft fractures. Operative treatment is expected to result in earlier recovery than non-operative treatment. Earlier functional recovery will result in a better quality of life of patients, earlier work and ADL resumption, a higher level of independency, and less health care needs. Although costs for initial treatment will be higher in the operative group (due to surgery), we hypothesize that costs will be saved by less health care needs during the recovery process and less productivity loss. Despite higher initial costs, we expect that primary surgery will be more cost-effective. To the best of our knowledge, this is the first high-quality multicenter prospective observational study that will look at patient, medical and societal perspective in patients with a humeral shaft fracture.

Thirty hospitals in the Netherlands will participate. Inclusion of patients has started October 01, 2012 and the expectation is to include 10 patients per month. With a follow-up of one year the presentation of data will be expected in the beginning of 2016.

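### 400 patients is ample for the primary DASH contrast, but the subtype claim used to justify it is unsupported, its recruitment schedule contradicts the reporting date, and the attrition allowance is slightly short

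*Protocol article*

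**What the plan says.** All but the schedule is in the protocol article, Sample size calculation.

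- **Primary calculation.** It assumes that "the mean DASH in the non-operative group will be 16, with a Standard Deviation (SD) of 16", against a mean of 10 with SD 10 in the operative group at three months. It concludes: "A two-sided test with an α level of 0.05 and a β level of 0.2 requires 78 patients in every group".
- **Attrition.** For 10% mortality and a further 10% lost to follow-up, it states that "a sample size of 95 patients per group is needed".
- **Subtype requirement.** To judge whether functional scores differ between fracture subtypes, it says that "a minimum of 2x20 patients per fracture subtype is sufficient", and on that ground sets at least 200 patients in each treatment group. It gives no difference to detect, SD, power or number of subtypes for this step. The only other remark on 400 is that it will be more than enough for propensity matching, with an admission that the losses in matching are unknown.
- **Schedule (Discussion).** Inclusion began on 1 October 2012, "the expectation is to include 10 patients per month", and with one year of follow-up "the presentation of data will be expected in the beginning of 2016". Study procedures gives the last visit a window of 12 to 14 months.

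**The concern.** The move from 95 to 200 per group rests on the subtype sentence, and nothing shown supports its claim of sufficiency. Twenty per cell is about a quarter of the 78 per group that the same section needs for 80% power at 6 points. A published statement that the number suffices invites readers to take a non-significant subtype comparison as evidence that fracture type does not matter.

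The schedule is a separate problem: target, rate and reporting date cannot all be true. A reader cannot tell which was meant to give way, nor from the article alone whether the report will rest on complete 12-month data.

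The attrition figure is a small slip. Applying the stated losses to 95 does not leave 78.

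**Working it through.** **Inputs.** From Sample size calculation: means 16 and 10, SDs 16 and 10, two-sided α 0.05, power 80%, losses 10% + 10%, 2×20 per subtype, 200 per group. From Discussion: start 1 October 2012, 10 per month, one year of follow-up, data in early 2016. From Study procedures: 12–14 month window.

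**1. The plan's own figure.**
n = (1.960 + 0.842)² × (16² + 10²) / 6² = 77.6, so 78 per group. This reproduces.

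**2. The target of 200 per group for the primary contrast.**
After 20% loss, 200 × 0.8 = 160. SE = √(356/160) = 1.49, and 6/1.49 = 4.02. Power ≈ Φ(4.02 − 1.96) ≈ 98%.

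**3. The 2×20 claim.** The average SD is √((256 + 100)/2) = 13.34. The section gives no subtype difference, so 6 points is an assumption borrowed from the overall treatment effect. Power and detectable differences are for a two-sample t-test.

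| Comparison | n | SD | SE of difference | Power for 6 points | Detectable at 80% power |
|---|---|---|---|---|---|
| Subtype vs subtype, both treatments | 40 vs 40 | 13.34 | 2.98 | 51% | about 8.5 points |
| Subtype vs subtype, operative only | 20 vs 20 | 10 | 3.16 | 46% | about 9.1 points |
| Subtype vs subtype, non-operative only | 20 vs 20 | 16 | 5.06 | 21% | about 14.5 points |
| Operative vs non-operative within one subtype | 20 vs 20 | 13.34 (average of 16 and 10) | 4.22 | 28% | about 12 points |

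Each SE is SD × √(2/n). None of these readings reaches 80%, even before any allowance for several subtype comparisons. If the 20 is counted before loss, 16 per cell remain, and the within-subtype figures become about 23% power and 13.7 points.

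**4. Schedule.**
- 400 / 10 = 40 months from 1 October 2012, which is the end of January 2016.
- Adding 12 to 14 months puts the last visits in January–March 2017.
- Working back from the start of 2016, one year of follow-up requires the last enrolment by about the end of 2014. That is 27 months of accrual: 27 × 10 = 270 patients, or 68% of 400.
- Reaching 400 in 27 months needs 400 / 27 = 14.8 per month.

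**5. Attrition.**
- Losses in sequence: 78 / (0.9 × 0.9) = 96.3, so 97.
- Losses added: 78 / 0.8 = 97.5, so 98.
- The stated 95 matches 78 × 1.1 × 1.1 = 94.4, which multiplies up by the loss rate instead of dividing by the retained share.
- 95 leaves 95 × 0.80 = 76 or 95 × 0.81 = 77. By the normal approximation, power is then 79.2–79.7%, against 80.2% at 78.

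**The case against.** The strongest reply is that none of this threatens the main question. That stands. The 78 is right and 400 gives wide margin for the primary contrast, so a reader should not infer that the trial is too small or that the sample size as a whole fails.

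A reader might also seize on 28% as the power of the subtype analysis. The documents do not support that. The sentence concerns differences between subtypes, whereas 28% is for treatment within one subtype and borrows the overall effect. The closer reading is 40 vs 40 at about 51%, and that too depends on an assumed 6 points. In addition, 20 is stated as a minimum, so commoner subtypes will have more. The primary analysis is a mixed model over time, not a single-visit t-test. The subtype frequencies that lead from 2×20 to 200 come from a retrospective study not shown, so any loss margin in that step cannot be checked. These points mean that no stated subtype power calculation is contradicted. They do not supply the missing basis for calling the number sufficient.

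On the schedule, a reader might infer that only about two thirds of the cohort will be analysed, or that patients will be reported without 12-month data. The documents do not say so. Recruitment runs to a number, no calendar data cut is set, and rate and date are given as expectations in the Discussion. On the plan's own rule the date would slip. The three figures still contradict each other.

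On attrition, the shortfall is 2 to 3 patients and is overtaken by the 200 per group set in the next paragraph.

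**Conclusion.** The concern holds in limited form. The primary calculation and the adequacy of 400 for it stand. What needs correcting, in order of weight:

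1. **Subtype justification.** The claim has no stated effect or power behind it. At a difference equal to the plan's own overall effect, power is between about 21% and 51% depending on the reading. At the minimum cell sizes, 80% power is reached only at about 8.5 points (subtype vs subtype, 40 vs 40) or 12 points (treatment within a subtype). This rests on the plan's SDs holding within subtypes, on the assumed 6 points, and on a single-visit comparison.
2. **Schedule.** Target, rate and date conflict by about a year. This needs no assumption beyond the stated figures.
3. **Attrition.** 95 should be 97 or 98. The cost is about 1 point of power, with no effect on the 400 target.

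The stated ground for 400 is wrong as written, not the number itself. The correction is worthwhile but does not affect the validity of the primary comparison.

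**What to change.** - **Subtypes.** Replace the sufficiency claim with the detectable differences: about 8.5 DASH points between two subtypes at 40 vs 40, and about 12 points for treatment within a subtype at 20 vs 20, with the SDs used. Report subtype comparisons as exploratory estimates with confidence intervals, and say that a non-significant result is not evidence of no difference.
- **Target.** Justify 400 by the precision of the primary contrast: about 160 evaluable per group, SE about 1.5 points, about 98% power for 6 points.
- **Schedule.** Reconcile target, rate and date. At 10 per month, reporting falls in 2017; keeping early 2016 needs about 15 per month. State that the final analysis waits for the 12-month visit of the full cohort.
- **Attrition.** Change 95 to 97 (78/0.81) or 98 (78/0.80) and say which loss model is meant.

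The cost is a few restated sentences, and a later reporting date if the rate stays at 10 per month. No extra patients, visits or data are needed.
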